**Fig. 1 Fig1:**
[figure not shown]
Study design diagram

For weaning from MV in both groups, patients will be assessed daily for readiness for a spontaneous breathing trial based on the ARDSNet protocol [25].

### General procedures

All participating patients, regardless of the study arm into which they are randomized, will be monitored and managed following general standard of care practices aimed at maintaining optimal conditions. Data from lung mechanics, gas exchange, and hemodynamics will be collected on days 0, 1, 3, 6, and 10, and every 7 days, including the last day of MV (Fig. 2). On each day, the lowest and the highest values of each of the following parameters will be recorded: (i) MV and gas-exchange parameters, including V_T_ (ml/kg PBW), respiratory rate, plateau pressure, PEEP, PaO_2_/FiO_2_, PaCO_2_; (ii) hemodynamics, including blood pressure, heart rate, need for vasoactive drugs; (iii) safety, including frequency of complications (barotrauma, sepsis, pneumonia, etc.), routine biochemistry and hematological tests; (iv) critical care severity scores recorded on days 0 and 1, such as acute physiology and chronic health evaluation II (APACHE II) score [26] and lung injury severity score [27]; (v) total number of extrapulmonary organ failures included in the sequential organ failure assessment (SOFA) scale [28] will be documented daily. Any organ failure occurring during the 6-hour period before death will be considered part of the terminal event and not counted [29]. We will use standard definitions for sepsis and organ failures [28, 30, 31]. We will also monitor ICU and hospital mortality, and duration of MV. Patients will be followed up for 60 days after enrollment.

**Fig. 2 Fig2:**
[figure not shown]
Schedule of events

### Primary and secondary outcomes

The primary outcome of interest is the number of ventilator-free days (VFDs) at 28 days [32], defined as days alive and free from MV at day 28 after intubation. For subjects ventilated ≥ 28 days and for subjects who die, VFD is 0. The secondary outcome of interest is all-cause 60-day mortality.

### Sample size calculations and interim analysis

Since there are no previous pharmacologic studies in patients with persistent ARDS, we estimated the sample size on the assumption that dexamethasone could increase VFDs by ≥ 2 days (from an estimated reference VFDs of 9 days), or would reduce overall 60-day mortality by ≥ 15 % (from a reference control mortality of 50 %). Depending on the estimated standard deviation for the mean VFDs and the expected 60-day mortality rate, we studied various group-size scenarios with cohorts of 147 to 157 patients in each arm to detect these differences with a power of 80 % and a type 1 error of 5 % (two-sided). A population size of 157 patients for each arm (a total of 314 patients) will satisfy all scenarios. No patient loss has been considered. We will only analyze patients that are enrolled and randomized. The power analysis has been performed according to Schoenfeld et al [32] (Fig. 3). Since we need three probabilities for estimating VFD and sample size (Table 1, highlighted in *yellow*), we selected three probabilities compatible with our hypothesis (using the Mann-Whitney test).

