**Fig. 3 Fig3:**
[figure not shown]
Estimation of samples size calculations based on expected ventilator-free days and mortality. Power analysis has been performed according to Schoenfeld et al [32]. Since we need three probabilities (see Table 1, text highlighted in *yellow*), we have selected three probabilities compatible with our hypothesis (using Mann-Whitney test). We hypothesized that patients in the experimental treatment group have a greater probability of being weaned earlier from the ventilator (0.0641 vs. 0.481) and a lower probability of dying (0.0345 vs. 0.05) for each day of the follow-up period

**Table 1 Tab1:** Calculations for the sample size

	VFDs		Probability of getting off ventilation alive	Probability of death	Probability of receiving ventilation	Expected mortality
	Mean	SD	pa	pd	po	60-day mortality
Control group	9.0	10.7	0.0481	0.0500	0.9019	0.4814
Experimental group	12.0	10.8	0.0641	0.0345	0.9014	0.3308
Difference	3.0		0.0160	-0.0155	-0.0005	-0.1506

*VFD* ventilator-free days, *SD* standard deviation

There will be one single formal interim analysis for both efficacy and futility. This analysis will be performed once 50 % of the planned patients have been randomized and initiated treatment and have been followed up to day 60. To protect against an obvious lack of efficacy, failure to achieve an increase of VFDs ≥ 1 day will justify stopping the trial. To protect against a clear improvement of efficacy, achieving a statistically significant difference in VFDs ≥ 3 days or an absolute difference in 60-day mortality ≥ 15 % (two-tailed significant difference *p* < 0.025) will justify stopping the trial. The interim analysis will be performed at the coordinating center (Hospital Universitario [name], Las Palmas de Gran Canaria, Spain) by an external, independent data and safety monitoring board. Investigators enrolling patients will be blinded to the results of this interim analysis if the stopping rule is not applied.

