### Statistical analysis of data

Data will be collected in each participating ICU using a standardized form. Data will be transmitted to the coordinating center whenever a patient dies or is discharged from the hospital. Before exporting the data into a computerized database at the coordinating center, a trained data collector from the coordinating center will check the completeness and the quality of information. Logical checks will be performed for missing data and to find inconsistencies, especially regarding clinical diagnosis, date, and severity scores. If necessary, the data collector will contact the investigator by phone to validate the data or reformat the data for entry into the database.

The primary endpoint is the number of ventilator-free days (VFDs) to day 28 after intubation, where all deaths will be awarded zero days. The analysis of VFDs will be performed as intention to treat. By definition, all patients will be mechanically ventilated at the time of ARDS onset. Secondary endpoint is mortality at 60 days (the patient could die before that time period, or could be alive in the ICU, in the hospital or at home). Other outcome endpoints include pulmonary complications (barotrauma), duration of MV, number of extrapulmonary organ failures, and hospital mortality.

Descriptive statistics will be expressed as mean ± SD or median and interquartile range, depending on the nature and distribution of the variables. Inferential statistics will use estimates of the mean of the differences and their 95 % confidence intervals. Variables normally distributed will be compared with the Student’s *t* test. For variables without a normal distribution, the Mann-Whitney *U* rank test will be used for comparison. Categorical variables will be compared using Fisher’s exact test. Probability of survival at 60 days after randomization will be analyzed according to the Kaplan-Meier method, and the results compared with the log-rank test. The relative risks and their 95 % confidence intervals will be estimated. For all these comparisons, we will consider a difference to be statistically significant if *p* < 0.05 (two-sided).

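### With 157 patients per arm, power for ventilator-free days is about 69–70% for the 3-day gain in Table 1 and about 38% for the 2-day gain in the text, not 80%

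*Protocol article*

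**What the plan says.** In the protocol article, the section on sample size calculations and interim analysis sets the VFD effect as follows: "dexamethasone could increase VFDs by ≥ 2 days (from an estimated reference VFDs of 9 days". As an alternative it names a 15% reduction in 60-day mortality from a control rate of 50%. It says that scenarios with 147 to 157 patients per arm were examined "to detect these differences with a power of 80 % and a type 1 error of 5 % (two-sided", and concludes: "A population size of 157 patients for each arm (a total of 314 patients) will satisfy all scenarios".

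Table 1 shows the calculation. Its rows give mean VFDs, SD, the three daily probabilities (off ventilation alive, death, still ventilated) and expected mortality:

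- "Control group 9.0 10.7 0.0481 0.0500 0.9019 0.4814"
- "Experimental group 12.0 10.8 0.0641 0.0345 0.9014 0.3308"

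The printed difference in mean VFDs is 3.0 days. The legend of Fig. 3 says of the inputs: "we have selected three probabilities compatible with our hypothesis (using Mann-Whitney test".

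The section on statistical analysis fixes the final test level: "we will consider a difference to be statistically significant if *p* < 0.05 (two-sided".

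**The concern.** Two things do not fit. The text plans for a gain of at least 2 days, while Table 1 works with 3. And with SDs near 10.7, a difference of 2 or even 3 days is small for 157 patients per arm: 3/10.75 is 0.28 of an SD, and 2/10.75 is 0.19.

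VFDs are the primary endpoint, so the 80% is the central quantitative claim of the design. If it is wrong, the chance of missing a real 2-day gain is about 62% rather than 20%. A reader who trusts the stated power could then take a non-significant result as evidence against a benefit that the trial had little chance of detecting.

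**Working it through.** **Inputs.** From Table 1: means 9.0 and 12.0, SDs 10.7 and 10.8; daily probabilities of coming off ventilation alive (pa) 0.0481 and 0.0641, of death (pd) 0.0500 and 0.0345, of staying ventilated (po) 0.9019 and 0.9014. From the sample size text: 2-day gain, 157 per arm, two-sided 5%, 80% power, no losses.

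**Step 1. Reproduce Table 1.** Let a patient come off ventilation alive on day t (t = 1 to 28) with probability pa × po^(t−1) and then score 28 − t; everyone else scores 0. This gives:

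| Arm | Mean (SD), recomputed | Mean (SD), Table 1 |
|---|---|---|
| Control | 9.01 (10.72) | 9.0 (10.7) |
| Experimental | 11.97 (10.83) | 12.0 (10.8) |

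The agreement after rounding shows that this is the plan's own model and that its VFD means and SDs are sound.

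**Step 2. Power by normal approximation.**

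SE = √[(10.7² + 10.8²)/157] = √(231.13/157) = 1.213 days.

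Power = Φ(d/SE − 1.96):

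- d = 3: Φ(2.473 − 1.96) = Φ(0.513) = 69.6%
- d = 2: Φ(1.648 − 1.96) = Φ(−0.312) = 37.8%

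At 147 per arm, the lower end of the stated range, power is 66–67% for 3 days and about 36% for 2 days.

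**Step 3. Power with the named test.** A tie-corrected Mann-Whitney test on the Table 1 distributions gives 68.7% analytically and 69.0% in 10,000 simulated trials. For a 2-day gain the plan gives no daily probabilities, so they must be assumed:

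| Route to a 2-day gain | pa | pd | Power at 157 per arm |
|---|---|---|---|
| Both shifted in Table 1 proportions | 0.0589 | 0.0395 | 38.3% |
| Weaning only | 0.0644 | 0.0500 | 35.7% |
| Death only | 0.0481 | 0.0177 | 46.9% |

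**Step 4. What 80% would need.** With 1.96 + 0.8416 = 2.8016:

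- n per arm = 231.13 × 2.8016²/d² = 201.6 for d = 3 and 453.5 for d = 2, so 202 and 454. By Mann-Whitney, about 205 for the Table 1 effect and 443 for 2 days (both probabilities shifted).
- Gain detectable with 157 per arm: 2.8016 × 1.213 = 3.4 days.
- Common SD at which 157 per arm would give 80% for 2 days: 2/(2.8016 × √(2/157)) = 6.3.

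**Step 5. Mortality, since the claim covers every scenario.** Reading the 15% as absolute, in line with the −0.1506 in Table 1, and using the usual two-proportion formula with pooled variance under the null:

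- 50% versus 35%: Φ[(0.15 × √157 − 1.96 × √(2 × 0.425 × 0.575))/√(0.25 + 0.2275)] = Φ(0.737) = 76.9%; 170 per arm needed.
- 48.14% versus 33.08%: 77.8%; 166 per arm needed.

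**Step 6. Where 157 may come from.** With a one-sided 5% test and d = 3, power is Φ(2.473 − 1.645) = 79.6%, and the required size is 158 to 161 per arm over SDs 10.7 to 10.8. None of the two-sided calculations tried gave 157.

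**The case against.** The strongest reply concerns the 2-day figure. The plan prints no SD or daily probabilities for a 2-day gain. It says that the group size depended on the estimated SD, and it points to Fig. 3, which is not available here. The 38% therefore carries over the Table 1 SDs, and other routes to a 2-day gain give 36–47%. This is a fair reason to quote a range. It does not restore 80%, which would need an SD near 6.3 when the only SDs given are 10.7 and 10.8.

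One can also say that a 3-day gain satisfies a condition of at least 2 days, so that text and table do not strictly conflict. But a power claim for at least 2 days is normally read as holding at 2, and the 3-day case fails on printed values alone, with no help needed from Fig. 3 or an unseen analysis plan. Scoring conventions do not close the gap: starting the day count one day differently gives about 69%, and ranking deaths below patients still ventilated, which the plan does not do, gives 72.3%.

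Finally, the plan promises mean differences with 95% confidence intervals, which would show a careful reader whether 2 days is excluded. That reduces the risk of misreading a null result. It does not make the stated power correct.

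**Conclusion.** The point holds, and the statement must be corrected. At two-sided 5% with 157 per arm, power for the primary endpoint is about 69–70% for the 3.0-day gain of Table 1. This rests only on printed inputs. For a 2-day gain it is about 38% (36–47% by the route to the gain), on the assumption that the SDs and daily-probability model of Table 1 carry over. Power of 80% is reached only at about 3.4 days. The mortality scenario comes close but also misses 80%, at 76.9–77.8%.

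These figures assume no losses and the full 5% at the final analysis. Any alpha spent at the interim efficacy look would lower them slightly. That the size came from a one-sided calculation is a plausible explanation, not an established one.

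**What to change.** Keep 314 patients and correct the sample size section:

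1. Use one planning effect in text and table: the 3.0 days of Table 1.
2. State that 157 per arm gives about 69–70% power for 3 days and about 38% for 2 days at two-sided 5%, and that 80% is reached only for a gain of about 3.4 days.
3. Delete the sentence "A population size of 157 patients for each arm (a total of 314 patients) will satisfy all scenarios", and give the mortality power as about 77–78%.
4. State that a non-significant VFD result does not exclude a 2-day gain.
5. Have the sponsor check whether a one-sided calculation was labelled two-sided.

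This costs a wording change and a less favourable stated power, with no extra patients. If the sponsor wants to keep the 80% claim for 3 days instead, the price is about 202–205 per arm: 404–410 in total, or 90–96 more patients than planned.

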**Fig. 3 Fig3:**
[figure not shown]
Estimation of samples size calculations based on expected ventilator-free days and mortality. Power analysis has been performed according to Schoenfeld et al [32]. Since we need three probabilities (see Table 1, text highlighted in *yellow*), we have selected three probabilities compatible with our hypothesis (using Mann-Whitney test). We hypothesized that patients in the experimental treatment group have a greater probability of being weaned earlier from the ventilator (0.0641 vs. 0.481) and a lower probability of dying (0.0345 vs. 0.05) for each day of the follow-up period

**Table 1 Tab1:** Calculations for the sample size

	VFDs		Probability of getting off ventilation alive	Probability of death	Probability of receiving ventilation	Expected mortality
	Mean	SD	pa	pd	po	60-day mortality
Control group	9.0	10.7	0.0481	0.0500	0.9019	0.4814
Experimental group	12.0	10.8	0.0641	0.0345	0.9014	0.3308
Difference	3.0		0.0160	-0.0155	-0.0005	-0.1506

*VFD* ventilator-free days, *SD* standard deviation

There will be one single formal interim analysis for both efficacy and futility. This analysis will be performed once 50 % of the planned patients have been randomized and initiated treatment and have been followed up to day 60. To protect against an obvious lack of efficacy, failure to achieve an increase of VFDs ≥ 1 day will justify stopping the trial. To protect against a clear improvement of efficacy, achieving a statistically significant difference in VFDs ≥ 3 days or an absolute difference in 60-day mortality ≥ 15 % (two-tailed significant difference *p* < 0.025) will justify stopping the trial. The interim analysis will be performed at the coordinating center (Hospital Universitario [name], Las Palmas de Gran Canaria, Spain) by an external, independent data and safety monitoring board. Investigators enrolling patients will be blinded to the results of this interim analysis if the stopping rule is not applied.

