### Enrollment into the study and randomization

For the present study, onset of ARDS was defined as the day and time in which the patient first met ARDS criteria [22, 23]. Screened patients will be considered for enrollment immediately prior to randomization and to the first dose of study medication on day 1 if they still meet the ARDS inclusion criteria at 24 hours after ARDS onset, assessed on standard ventilator settings. Arterial blood gases and hemodynamic and data will be obtained on the following mandatory standard ventilator settings: volume assist/control mode, V_T_ 7 ml/kg predicted body weight (PBW), inspiratory:expiratory (I:E) time ratio 1:1, ventilator rate to maintain a partial pressure of carbon dioxide (PaCO_2_) of 35 to 50 mm Hg, on FiO_2_ ≥ 0.5 and PEEP ≥ 10 cmH_2_O) [24]. If under these ventilator settings, the PaO_2_/FiO_2_ is ≤ 200 mmHg, the patient will be eligible for randomization.

Eligible, informed consented patients will be randomly allocated to two arms: (i) conventional treatment without dexamethasone and (ii) conventional treatment plus dexamethasone. Randomization will be performed by blocks of ten opaque, sealed envelopes sent to each participating ICU, according to a computer-generated random-number table. Randomization will be based on one-to-one allocation of prenumbered envelopes. As requested, a second block of ten sealed envelopes will be sent to those participating ICUs with high enrollment rates.

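### The 1-day futility cut is missed 28% (2-day gain) or 12% (3-day gain) of the time by a drug that works as assumed, and the stated 80% power leaves this out

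*Protocol article*

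**What the plan says.** All of this stands in the protocol article, under Sample size calculations and interim analysis.

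- **Assumed effect.** The text assumes that "dexamethasone could increase VFDs by ≥ 2 days (from an estimated reference VFDs of 9 days"), or that 60-day mortality falls by at least 15% from 50%. Table 1 works with a larger VFD gain: "Control group 9.0 10.7" against "Experimental group 12.0 10.8" (mean, SD), a difference of 3.0 days.
- **Power.** Cohorts of 147 to 157 per arm were studied "to detect these differences with a power of 80 % and a type 1 error of 5 % (two-sided"), and "A population size of 157 patients for each arm (a total of 314 patients) will satisfy all scenarios". The calculation is a fixed-sample one for the Mann-Whitney test.
- **Interim.** There is one look, when half of the planned patients have reached day 60. The futility clause reads "To protect against an obvious lack of efficacy, failure to achieve an increase of VFDs" of at least 1 day, and says that this justifies stopping. The efficacy clause names both VFDs (at least 3 days and significant) and 60-day mortality (at least 15% absolute), with p < 0.025.

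Nothing ties the sample size or the power to the futility clause. No probability of a wrong stop is given, and the clause is not declared binding or non-binding.

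**The concern.** The clause is presented as guarding against a plain absence of effect, but it is a bare point estimate taken where the standard error is larger than the cut itself. An observed gain below 1 day is then an ordinary result for a drug that delivers what the protocol assumes.

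Two things follow. First, a power figure that ignores a rule able to end the trial early cannot be the power of the design as written. Second, the trial was sized on VFDs or mortality, and mortality can trigger an efficacy stop, yet the futility clause refers to VFDs only. Applied mechanically, it could end a trial that was heading for a significant mortality result.

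**Working it through.** **Inputs.** SDs 10.7 and 10.8, and the daily probabilities (Table 1). Gains of 2 days (text) and 3 days (Table 1). 157 per arm, 1:1, two-sided 5% (text). Interim at 50%, so 157/2 = 78.5 per arm. Assumptions: normal approximation, interim estimate taken as the difference in means, equal arms at the interim.

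**Step 1: the plan's own figures.** Table 1's daily probabilities give VFD means and SDs of 9.01 (10.72) and 11.97 (10.83), so its VFD columns reproduce. The 157 per arm does not: 80% two-sided power needs 450 to 458 per arm for 2 days and 200 to 204 for 3 days (about 206 by Mann-Whitney).

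**Step 2: interim precision.** SE = sqrt((10.7² + 10.8²)/78.5) = sqrt(231.13/78.5) = 1.716 days. The cut is at Z = 1/1.716 = 0.583.

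**Step 3: probability of a futility stop.** P(stop | δ) = Φ((1 − δ)/1.716).

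- δ = 2: Φ(−0.583) = 0.280
- δ = 3: Φ(−1.166) = 0.122
- δ = 0: Φ(0.583) = 0.720

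A simulation of 10,000 trials from Table 1's daily probabilities gave 12.2% at the Table 1 effect; the matching check at 2 days gave 28.6%.

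**Step 4: VFD power with and without the rule.** The final SE is sqrt(231.13/157) = 1.213. Fixed-sample power is Φ(δ/1.213 − 1.96). Power with the rule is P(interim difference ≥ 1 and final Z > 1.96), with correlation sqrt(0.5).

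| True gain | No rule | With rule | Loss |
|---|---|---|---|
| 2 days | Φ(−0.312) = 37.8% | 35.9% | 1.9 points |
| 3 days | Φ(0.513) = 69.6% | 67.2% | 2.4 points |

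Adding the VFD efficacy stop hardly changes this: with both rules, power is 38% and 69%. If the SD were small enough for 157 per arm to give exactly 80% (about 6.3 days for a 2-day gain, 9.5 for a 3-day gain), the rule would lower power to 73.8% (stop risk 16%) and 77.3% (stop risk 9%).

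**Step 5: conditional power at an observed gain of exactly 1 day.** CP = 1 − Φ((1.96 − 0.583·√0.5 − 0.5·δ/1.213)/√0.5).

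- 3 days: (1.96 − 0.412 − 1.236)/0.7071 = 0.441, CP = 33%
- 2 days: (1.96 − 0.412 − 0.824)/0.7071 = 1.024, CP = 15%
- observed trend (1 day): (1.96 − 0.412 − 0.412)/0.7071 = 1.607, CP = 5%

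**Step 6: 60-day mortality.** Trials were simulated from Table 1's daily probabilities (157 per arm, interim at 78 per arm, no deaths after liberation from the ventilator). Run to day 60, these probabilities give about 50.9% against 34.9%. The printed 48.14% and 33.08% are what they give at day 28.

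| Mortality rates | Test | No rule | Rule applied mechanically |
|---|---|---|---|
| Daily probabilities to day 60 | chi-square | about 81% | about 75% |
| Daily probabilities to day 60 | Fisher | about 78% | about 73% |
| Table 1 printed rates | chi-square | about 78% | about 73% |
| Table 1 printed rates | Fisher | about 75% | about 70% |

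In the first row, about 46% of the stopped trials would have reached a significant mortality benefit had they continued.

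**Step 7: a cut at 0 days, for comparison.** P(stop) = Φ(−δ/1.716): 12% at 2 days, 4% at 3 days, 50% at no effect.

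**The case against.** **A high stop probability is not the same as lost power.** A reader might infer from 28% and 12% that the rule throws away that much chance of success. It does not. Most of the stopped trials would have missed significance on VFDs anyway, and the loss on the primary endpoint is about 2 points. This objection stands and limits the point.

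**The cut is not wrong in itself.** A reader might infer that 1 day should be replaced by 0. But 1 day corresponds to 15% conditional power under the 2-day effect, and 0 days to the same 15% under the 3-day effect. The protocol states both effects, so the choice between the cuts is a choice of reference effect. The lower cut also has a price: an ineffective drug is stopped 50% rather than 72% of the time. This stands as well.

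**The rule may not bind.** The clause says that the result justifies stopping. The next sentences allow for the rule not being applied, and Trial organization gives the board a recommending role. All the losses above assume mechanical stopping and are upper bounds. The text never settles the matter, though, and that is what needs fixing.

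**Mortality is not wholly ignored.** Deaths score zero VFDs, so a survival benefit raises the monitored quantity. Nothing forbids the board from looking at day-60 deaths, and mortality is a secondary outcome. That is fair, but it does not remove the loss: the simulation already scores deaths as zero and still shows about 4 to 6 points.

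**The larger power problem lies elsewhere.** This is true. Without any interim, 157 per arm gives about 38% at 2 days and 69 to 70% at 3 days. That is a separate defect and does not make the futility clause consistent with the stated 80%.

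**Conclusion.** The point holds in a limited form. With Table 1's SDs and 157 per arm, the 1-day cut sits at Z = 0.58 and would be missed 28% of the time at a true 2-day gain and 12% at 3 days, so missing it is not evidence of a plain lack of efficacy. The stated 80% power takes no account of the rule. At 2 days, if the rule is applied, 80% cannot hold, because a 28% false-stop risk already exceeds a 20% type II error.

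The cost in power is modest: about 2 points on VFDs at either effect, and about 4 to 6 points on 60-day mortality. The mortality loss arises because the clause names only VFDs.

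The documents do not support the stronger conclusions that the rule badly damages the primary analysis, that the threshold is an error, or that the board is bound to stop. The figures rest on Table 1's SDs and daily probabilities, on the assumptions listed with the calculations, and on mechanical application of the rule.

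**What to change.** Under Sample size calculations and interim analysis:

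1. State that the futility rule is non-binding, and that the board must weigh interim 60-day mortality before recommending a futility stop. Every patient in the interim analysis will already have been followed to day 60, so no new data are needed.
2. Restate the power net of the rule for both the 2-day and the 3-day gain, and report the false-stop probabilities (28% and 12%), with 72% for a drug without effect.

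The cost is wording and one recalculation, best done together with the correction of the sample size. For scale, 80% power at 3 days needs about 217 per arm with the rule applied, against 202 without it. A non-binding rule does not inflate the type I error, because the final test at 5% takes no credit for futility stops.

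The sponsor may also consider a cut near 0 days (false stop 12% at 2 days and 4% at 3 days), at the price of stopping an ineffective drug 50% rather than 72% of the time. That is a trade-off to decide and is not required to repair the text.

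### An efficacy stop is allowed at half information at p<0.025 on either of two endpoints, yet the final test keeps the full p<0.05, so the stated two-sided 5% type I error is not held unless the futility rule is binding

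*Protocol article*

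**What the plan says.** Three statements in the protocol article bear on this.

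- **Sample size calculations and interim analysis, first paragraph.** The group sizes are chosen "to detect these differences with a power of 80 % and a type 1 error of 5 % (two-sided").
- **Same section, after Table 1.** "There will be one single formal interim analysis for both efficacy and futility". On timing: "This analysis will be performed once 50 % of the planned patients have been randomized and initiated treatment", with follow-up to day 60. The efficacy rule opens "To protect against a clear improvement of efficacy, achieving a statistically significant difference in VFDs"; with its thresholds, the grounds for an efficacy stop are "achieving a statistically significant difference in VFDs ≥ 3 days or an absolute difference in 60-day mortality ≥ 15" %, with the level given as "two-tailed significant difference *p* < 0.025) will justify stopping the trial". For futility, a VFD gain below 1 day is likewise described as grounds for stopping.
- **Statistical analysis of data, last paragraph.** "For all these comparisons, we will consider a difference to be statistically significant if *p* < 0.05 (two-sided").

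VFDs to day 28 are the primary endpoint and 60-day mortality the secondary one. The Trial organization section says the data and safety monitoring board recommends continuing or stopping on the interim data. The article names no spending function, does not lower the final level, and does not divide the interim level between the two triggers.

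**The concern.** A trial that can claim efficacy at an interim look and again at the end has two chances of a false positive. Some of the 5% must be set aside for the first look, and here none is. The article fixes both thresholds, so this is not a detail left to an analysis plan that is not shown: the two numbers together conflict with the stated 5%. The interim look also offers a second route to an efficacy stop, through mortality, at the same p<0.025.

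At stake is how a borderline final result is read. A final VFD p-value just under 0.05 would be declared positive under a design that does not hold 5% at that threshold. The Discussion presents the trial as adequately powered to answer its question definitively, so a borderline result would carry weight.

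**Working it through.** **Inputs.** From the article: interim at 50% of 314 patients, about 78.5 per arm; interim level 0.025 two-tailed (critical value 2.241); final level 0.05 two-sided (1.960); Table 1 SDs 10.7 and 10.8; mortality 50% against 35%. Assumption, not in the article: the correlation rho between the VFD and mortality test statistics, shown from 0 to 0.9.

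**1. The plan's own figure.** A single final test gives P(|Z2|>1.960) = 0.05. The stated 5% is reproduced only if the interim look is ignored.

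**2. VFDs alone, futility non-binding.** The interim and final statistics have correlation √0.5 = 0.707.

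- Two-sided interim crossings: 0.025 + P(|Z1|≤2.241, |Z2|>1.960) = 0.025 + 0.0393 = **0.0643**.
- Benefit-direction interim stops only, two-sided final test: 0.0125 + P(Z1≤2.241, |Z2|>1.960) = 0.0125 + 0.0447 = **0.0572**. The benefit side is 0.0322, against 0.025 in a two-sided 5% test.
- If the 0.025 in parentheses governs mortality only and interim VFDs are tested at 0.05: 1 − P(|Z1|<1.960, |Z2|<1.960) = 0.0831.

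**3. Interim stop on either endpoint, final test on VFDs.** Both endpoints use 2.241 at the interim.

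| rho | two-sided crossings | benefit-direction interim stops only |
|---|---|---|
| 0 | 8.8% | 6.9% |
| 0.5 | 8.4% | 6.7% |
| 0.7 | 8.0% | 6.5% |
| 0.9 | 7.3% | 6.2% |

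Hand check at rho = 0: 1 − (1 − 0.0643)(1 − 0.025) = 0.0877. Simulating null trials from the Table 1 control probabilities gives 6.2% to 6.6% for VFDs alone and 7.5% to 8.0% with either interim trigger, in line with the normal approximation.

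**4. Do the effect-size conditions help?**

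- VFDs: SE = √((10.7² + 10.8²)/78.5) = 1.716. Three days gives z = 3/1.716 = 1.75, p = 0.080. Reaching p<0.025 needs 2.241 × 1.716 = 3.85 days.
- Mortality, pooled rate 0.425: SE = √(2 × 0.425 × 0.575/78.5) = 0.0789. Fifteen points gives z = 1.90, p = 0.057. Reaching p<0.025 needs 2.241 × 0.0789 = 0.177, or 17.7 points (17.9 with a rate of 0.5).

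Any result with p<0.025 already clears 3 days or 15 points, so neither condition lowers the error.

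**5. If the futility rule were binding.** A gain of 1 day is z = 1/1.716 = 0.58. Requiring the trial to stop below that gives a total error of about 3.0% for VFDs alone, and 3.5% (rho 0.9) to 4.2% (rho 0) with the mortality trigger. For VFDs alone, all but a trace of the 3.0% lies on the benefit side.

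**6. Final level that restores 5%.**

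- VFDs as the sole trigger at 0.025: final z = 2.125, p = 0.0336.
- O'Brien-Fleming: 2.797 then 1.977, p = 0.005 then 0.048.
- Both triggers at 0.025, two-sided crossings counted: a final VFD test at 0.0336 leaves 6.0% (rho 0.9) to 7.4% (rho 0). Solving the step 3 calculation for 5% gives a final level of about 0.021 (rho 0.9) down to 0.0016 (rho 0). Counting benefit-direction interim stops only, it gives about 0.037 to 0.029.

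**The case against.** The strongest reply is the futility rule. If a gain below 1 day must stop the trial, total error is below 5% (step 5), and on the article's own two-sided measure the excess disappears. This stands as a condition on the finding. It does not remove it: the article describes the shortfall as grounds for stopping, and the board only recommends, so the rule reads as non-binding and its protection cannot be credited. Even if it were binding, the benefit-side error would be about 3.0% against 2.5%.

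Second, the efficacy stop is meant for improvement only, so harm-direction interim crossings arguably should not count. That is fair, and is why 5.7% is given as the lower figure.

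Third, Fisher's exact test, prescribed for categorical variables, is conservative: at 78 per arm its actual size at a nominal 0.025 is about 0.020. The mortality contribution is therefore somewhat smaller than step 3 shows. The VFD-only figures are unaffected.

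A reader might go further in two ways that the document does not support:

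- One might quote 9% or more for a claim on either endpoint at either look. That counts a final win on mortality, which the article names as secondary, so it is not an error on the primary claim.
- One might say that every final p between 0.034 and 0.05 is wrongly positive. That follows only from the 0.025/0.034 boundary; under O'Brien-Fleming the zone is only 0.048 to 0.05.

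**Conclusion.** The point holds. As written, the interim and final thresholds do not deliver the stated two-sided 5%. The excess on the primary endpoint is modest: 5.7% to 6.4%. With mortality as a second interim trigger and a final VFD test, the error is about 6.2% to 8.8%. If the interim VFD test is read at 0.05 rather than 0.025, VFDs alone give 8.3% with two-sided crossings, so the ambiguous parenthesis does not rescue the plan.

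These figures assume non-binding futility, half the information at the interim for both endpoints, and normal approximations. The two-endpoint range also rests on the assumed correlation of 0 to 0.9. A separate analysis plan could set a lower final level, but this article fixes 0.05 explicitly.

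**What to change.** Adopt one alpha-spending rule for VFDs and state the matching final level in the Statistical analysis section. Either keep p<0.025 at the interim and test the final at two-sided p<0.034, or use O'Brien-Fleming with about p<0.005 at the interim and p<0.048 at the end. State whether the interim level applies to both endpoints and whether futility is binding.

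Mortality may remain an interim efficacy trigger if it has its own alpha, taken out of the 5%. Otherwise, test it after VFDs in fixed sequence. The 3-day and 15-point conditions should not be relied on for error control.

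The 0.034 level holds 5% only when VFDs are the sole interim efficacy trigger. Enrolment began in March 2013 and the article does not say whether the interim has taken place. If it was run with both triggers at 0.025, derive the final level from both. With two-sided crossings counted, that level is stricter than 0.034 (step 6). Record the chosen level, and the correlation assumed for it, before final data are seen.

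The cost is a wording change, a slightly stricter final threshold and a small loss of power; the loss is larger if both triggers were already used.
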